##### Therapeutic part

According to the dose escalation scheme, a single therapeutic injection of 800 MBq/m^2^, or 1600 MBq/m^2^, or 2700 MBq/m^2^ or 4000 MBq/m^2^ of [^131^I]ICF01012 will be administered at D11 (± 4 days) under the same conditions as those for diagnostic injection (slow IV injection in approximatively 10 min).

Before therapeutic injection of [^131^I]ICF01012, patients will receive identical premedication as for the diagnostic injection: potassium iodide 130 mg at 48 h before infusion, loratadine 10 mg and potassium iodide 130 mg 24 h before injection. The day of the injection, oral potassium iodide 130 mg will be taken approximatively 4 h before injection and IV premedication (dexchlorpheniramine 5 mg and hydrocortisone hémisuccinate 500 mg) 5 minutes before injection. Thyroid blockade will be pursued for a period of 60 days (D12-D71) (potassium iodide 130 mg daily).

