#### Study procedures and participant timeline

The overview of study assessments and procedures is detailed in Table 1 for patients who participate only to the selection part, and in Table 2 for patients who participate to the selection part and the treatment part.

**Table 1 Tab1:** Assessment schedule for patients who received diagnostic injection and were not eligible to therapeutic part

TIMEPOINT	Screenig / baseline	Selection part			Follow-up period		
Week		W0			W1	W2	W3
Day	−30 to −1	D0	D1	D4	D7	D14 ± 4	D35 ± 4
Informed consent	✓						
Medical history and demographic	✓						
Prior / concomitant medication	✓	Collecting during all the study					
Adverse event evaluation	✓	Collecting during all the study					
Physical exam	✓	✓	✓	✓	✓	✓	✓
Vital signs	✓	✓before, 5 min, 30 min, 1 h, 3 h after	✓	✓	✓	✓	✓
Performance status OMS	✓	✓			✓	✓	✓
ECG	✓						✓
LVEF	✓						
Dermatologist consultation	✓					✓	
Ophthalmologist consultation	✓					✓	
Neurologist consultation	✓					✓	
Imaging acquisition for dosimetry		✓30 min, 1 h, 3 h after	✓	✓	✓		
Disease evaluation	✓						
Pregnancy test	✓						
Hematology and coagulation	✓			✓	✓	✓	✓
Blood chemistry	✓			✓	✓	✓	✓
Thyroid function	✓						✓
Urinalysis	✓					✓	✓
Pharmacokinetic sample		✓Before, 5, 10, 15, 30 min, 1 h, 3 h after	✓	✓	✓		
[131I]ICF01012		✓ 185 MBq

**Table 2 Tab2:** Assessment schedule for patients who received diagnostic and therapeutic injection

TIMEPOINT	Screenig / baseline	Selection part				Therapeutic part						Follow-up period				
Week		W0				W1					W2	W3	W5	W7	W10	W13
Day	−30 to −1	D0	D1	D4	D7	D11 ± 4	D12 ± 4	D13 ± 4	D15 ± 4	D16 ± 4	D18 ± 4	D25 ± 4	D39 ± 4	D53 ± 4	D74 ± 4	D96 ± 4
Informed consent	✓															
Medical history and demographic	✓															
Prior / concomitant medication	✓	Collecting during all the study														
Adverse event evaluation	✓	Collecting during all the study														
Physical exam	✓	✓	✓	✓	✓	✓	✓	✓	✓	✓	✓	✓		✓	✓	✓
Vital signs	✓	✓ before, 5, 30 min, 1 h, 3 h after injection	✓	✓	✓	✓ before, 5, 30 min, 1 h, 3 h after injection	✓	✓	✓	✓	✓	✓		✓		✓
Performance status OMS	✓	✓			✓	✓	✓	✓	✓	✓	✓	✓		✓		✓
ECG	✓													✓		✓
LVEF	✓															✓
Dermatologist consultation	✓											✓		✓		✓
Ophthalmologist consultation	✓				OCT							✓OCT				✓
Neurologist consultation	✓											✓				
Imaging acquisition for dosimetry		✓30 min, 1 h, 3 h after	✓	✓	✓				✓		✓	✓			✓	
Disease evaluation	✓															✓
Pregnancy test	✓															

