Hematology and coagulation	✓			✓	✓				✓	✓	✓	✓	✓	✓		✓
Blood chemistry	✓			✓	✓		✓		✓	✓	✓	✓	✓	✓		✓
Thyroid function	✓					✓							✓	✓		✓
Urinalysis	✓					✓	✓		✓	✓	✓	✓	✓	✓		✓
Pharmacokinetic sample		✓Before, 5, 10, 15, 30 min, 1 h, 3 h after														
[131I]ICF01012		✓ 185 MBq				✓ TI^a^										

^a^a single therapeutic injection (TI) of 800 MBq/m^2^, or 1600 MBq/m^2^, or 2700 MBq/m^2^ or 4000 MBq/m^2^ of [131I]ICF01012

Before any study-related assessment starts, written informed consent will be obtained for each patient. A screening/baseline visit will include imaging for disease evaluation and a dosimetric whole-body CT-scan within 30 days before administration of the diagnostic dose (D0). Within 15 days before administration of the diagnostic dose, the patients will have a clinical evaluation with vital signs, cardiac evaluation, specialized consultation with a dermatologist, a neurologist and an ophthalmologist, blood and urine test and a pregnancy test (for women of childbearing age).

Patients are registered before the diagnostic dose (D0).

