##### Selection part

For the selection part, patients will be able to stay hospitalized for 24 h after injection at their request. The diagnostic dose will be injected at D0 with a follow-up of vital signs: before, 5 min after the start of infusion, at the end of infusion, 30 min, 1 h, 3 h, and 24 h (D1) after end of infusion and then at D4 and D7.

The in vivo biodistribution of [^131^I]ICF01012 will be assessed using whole-body planar scintigraphy acquisition (30 min, 1 h, 3 h at D0, 24 h (at D1) 4 days (D4) and 7 days (D7) after injection) and Single Photon Emission Computed Tomography/Computed Tomography (SPECT-CT) acquisitions at 3 h (D0), 24 h (D1), 4 days after injection (D4) and SPECT at D7.

Blood samples for pharmacokinetic study will be collected at 5, 10, 15, 30 min, 1 h, 3 h (D0) 24 h (D1), 96 h (D4) and 168 h (D7) post-injection. A 24-h urine collection will be realized for hospitalized patients for excretion evaluation. Blood and urine tests for safety evaluation will be performed at D4 and D7.

The eligibility criteria for therapeutic part (at least one metastasis with [^131^I]ICF01012 uptake and an acceptable AD to major healthy organs) will be checked from D4 until D7 with dosimetry results. After verification of the eligibity criteria for therapeutic part, a dose allocation request will be done using an eCRF. Eligible patients for therapeutic phase will have an ocular optical coherence tomography (OCT) before therapeutic injection.

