##### Therapeutic part

A unique therapeutic injection of [^131^I]ICF01012 at a dose level of 800 MBq/m^2^, or 1600 MBq/m^2^, or 2700 MBq/m^2^ or 4000 MBq/m^2^ (according to dose escalation scheme), will be administered D11 ± 4 days with a follow-up of vital signs: before, 5 min after the start of infusion, at the end of infusion, 30 min, 1 h, 3 h, and 24 h (D12) after the end of infusion and then 2 days, 4 days, 5 days and 7 days after therapeutic dose. Patients will have to stay hospitalized between 3 and 7 days after injection, depending on received radioactivity, Patients will be discharged when 1-m rate of exposure reaches <40μSievert.h^− 1^.

The biodistribution of [^131^I]ICF01012 will be assessed using Whole-body planar scintigraphy acquisition (4 days (D15 ± 4 days), 7 days (D18 ± 4 days), 14 days (D25 ± 4 days), 63 days (D74 ± 4 days) after therapeutic injection) and SPECT-CT acquisition 4 days after injection (D15 ± 4 days) and SPECT at D77 days (D18 ± 4 days) 14 days (D25 ± 4 days), 63 days (D74 ± 4 days) after therapeutic injection. Blood and urine tests for safety evaluation will be performed 1 day, 4 days, 5 days and 7 days after therapeutic dose.

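### The only scheduled pregnancy test precedes the diagnostic dose; none is repeated before the therapeutic iodine-131 injection 8 to 30 days after that test

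*Protocol article*

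**What the plan says.** All references are to the protocol article.

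- **Exclusion criteria.** Pregnant women are excluded. Women of childbearing age must use effective contraception during treatment and for 12 months after the therapeutic dose.
- **Study procedures and participant timeline, baseline text.** The timing is "Within 15 days before administration of the diagnostic dose, the patients will have a clinical evaluation with vital signs", and the list that follows ends with "a neurologist and an ophthalmologist, blood and urine test and a pregnancy test (for women of childbearing age").
- **Table 2** (patients given both injections). The row labelled "Pregnancy test" has a single tick, under screening/baseline. Nothing is ticked at D0, D7, D11 or later. Table 1 also has one screening tick.
- **Study procedures, Selection part.** The check made from D4 to D7 covers "The eligibility criteria for therapeutic part (at least one metastasis with [^131^I]ICF01012 uptake and an acceptable AD to major healthy organs"). The one examination added before the injection is stated as: "Eligible patients for therapeutic phase will have an ocular optical coherence tomography (OCT) before therapeutic injection".
- **Study drug administration, Therapeutic part.** The therapeutic injection "will be administered at D11 (± 4 days) under the same conditions as those for diagnostic injection".
- **Secondary objectives.** The detailed blood and 24-h urine panels used for tolerance do not list hCG.

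**The concern.** The contraception rule runs from treatment until 12 months after the therapeutic dose, so the protocol itself treats that dose as the exposure that matters. The only test is nevertheless timed to the much smaller diagnostic dose. Several other baseline items (physical examination, vital signs, performance status, thyroid function, urinalysis) are ticked again at D11 ± 4 in Table 2, but pregnancy status is not.

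Two situations would escape the schedule as printed: a very early pregnancy that the screening test missed, and a conception between the test and the injection. In either case the larger iodine-131 activity could be given without anyone knowing. The harm to a fetus would be serious and could not be undone. The DLT definition, the choice of recommended dose and the analyses are not at stake.

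**Working it through.** The article states no interval from test to therapeutic injection, so there is no figure to reproduce. The interval follows from day arithmetic.

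**Inputs**
- Test: D−15 to D−1 (baseline text).
- Therapeutic injection: D11 ± 4, that is D7 to D15.
- Diagnostic activity: 185 MBq. Therapeutic levels: 800 to 4000 MBq/m².
- Body surface: not given; 1.5 to 2.0 m² is assumed.

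**Gap from test to injection** = injection day − test day

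| Case | Shortest | Longest |
|---|---|---|
| Injection on D11 | 11 − (−1) = 12 days | 11 − (−15) = 26 days |
| Full window D7 to D15 | 7 − (−1) = 8 days | 15 − (−15) = 30 days |
| Full window, test also allowed on D0 | 7 − 0 = 7 days | 30 days |
| Full window, only Table 2's D−30 to D−1 screening column applied | 8 days | 15 − (−30) = 45 days |

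The second row is the reading used here, because the text gives the narrower 15-day limit. These gaps run from the pregnancy test. The gap from the diagnostic dose to the therapeutic injection is 7 to 15 days.

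**Activity relative to the diagnostic dose**
- Lowest: 800 × 1.5 = 1200 MBq; 1200 / 185 = 6.5.
- Highest: 4000 × 2.0 = 8000 MBq; 8000 / 185 = 43.2.

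**Number exposed.** The Sample size section caps the therapeutic part at 18 patients. Women of childbearing age are an unstated fraction of these.

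**After the change.** With a negative result required on the injection day or within 72 h before it, the gap becomes 0 to 3 days.

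**The case against.** The strongest objection is that the article condenses an approved protocol (version 7), and a repeat hCG before therapeutic iodine-131 could sit there or in the nuclear-medicine site procedures. The absence would then be a reporting gap, not a design fault. This stands as a possibility and limits confidence. It does not remove the point: the article prints an assessment schedule with a row for this test and gives the timing in prose, so a single test is what it fixes.

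Second, Table 2 is known to drop ticks. Compared with the text, it lacks the pharmacokinetic samples at D1, D4 and D7, the urine tests at D4 and D7, the clinical examination and vital signs at D39, and the blood and urine analyses at D74. A missing tick alone is therefore weak evidence. In each of those cases, however, the text contradicts the table. Here the text places the test at baseline and mentions no other. It does not say in so many words that the test is done only once.

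Third, a baseline test with compulsory contraception over a short interval is a coherent, if minimal, safeguard, and no statement in the article is contradicted. That is fair: contraception remains the main protection. But it cannot reveal a pregnancy already present or a contraceptive failure.

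Fourth, the upper figures combine extremes: the earliest test with the latest injection, and the top dose level with a large assumed body surface. This is true, which is why the D11 figures and the lower ends are given as well.

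**Conclusion.** The concern holds. As printed, the schedule gives 800 to 4000 MBq/m² of iodine-131 with the last pregnancy test 8 to 30 days old (12 to 26 days for an injection on D11), and no listed step before the injection would detect a pregnancy. The day counts rest on the 15-day limit in the baseline text. The 6- to 43-fold activity ratio rests on the assumed body surface.

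The expected number affected is small, given at most 18 treated patients and mandatory contraception. The point should still be fixed because the possible harm is grave and the remedy is simple. Confidence is medium, since the full protocol was not available and may already contain the test.

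**What to change.** - **Table 2, pregnancy-test row:** add a tick at D11 ± 4.
- **Study procedures, Therapeutic part:** add a sentence such as: *In women of childbearing age, the therapeutic injection is given only after a negative hCG result obtained on the injection day or within 72 h before it.* The condition should attach to the injection, not to the dose-allocation request, which can come several days earlier.
- **Optional:** also run hCG on the D7 safety blood sample before the allocation request, so that most positives are found before a dose is prepared. This does not replace the test above, because D7 can be more than 72 h before the injection.
- **If the full protocol already has this test:** add it to the article's Table 2 and text.

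The cost is one routine assay for a few women and, rarely, a prepared dose that goes unused. No new visit is needed if the injection-day sample is used. Table 2 ticks thyroid function and urinalysis at D11 ± 4, so a sample should be available, although the therapeutic-part text lists its safety blood and urine tests only from one day after the injection. The sample must be taken and reported before the injection is given. No sample size, error rate or analysis changes.

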##### Selection part

For the selection part, patients will be able to stay hospitalized for 24 h after injection at their request. The diagnostic dose will be injected at D0 with a follow-up of vital signs: before, 5 min after the start of infusion, at the end of infusion, 30 min, 1 h, 3 h, and 24 h (D1) after end of infusion and then at D4 and D7.

The in vivo biodistribution of [^131^I]ICF01012 will be assessed using whole-body planar scintigraphy acquisition (30 min, 1 h, 3 h at D0, 24 h (at D1) 4 days (D4) and 7 days (D7) after injection) and Single Photon Emission Computed Tomography/Computed Tomography (SPECT-CT) acquisitions at 3 h (D0), 24 h (D1), 4 days after injection (D4) and SPECT at D7.

Blood samples for pharmacokinetic study will be collected at 5, 10, 15, 30 min, 1 h, 3 h (D0) 24 h (D1), 96 h (D4) and 168 h (D7) post-injection. A 24-h urine collection will be realized for hospitalized patients for excretion evaluation. Blood and urine tests for safety evaluation will be performed at D4 and D7.

The eligibility criteria for therapeutic part (at least one metastasis with [^131^I]ICF01012 uptake and an acceptable AD to major healthy organs) will be checked from D4 until D7 with dosimetry results. After verification of the eligibity criteria for therapeutic part, a dose allocation request will be done using an eCRF. Eligible patients for therapeutic phase will have an ocular optical coherence tomography (OCT) before therapeutic injection.

##### Therapeutic part

A unique therapeutic injection of [^131^I]ICF01012 at a dose level of 800 MBq/m^2^, or 1600 MBq/m^2^, or 2700 MBq/m^2^ or 4000 MBq/m^2^ (according to dose escalation scheme), will be administered D11 ± 4 days with a follow-up of vital signs: before, 5 min after the start of infusion, at the end of infusion, 30 min, 1 h, 3 h, and 24 h (D12) after the end of infusion and then 2 days, 4 days, 5 days and 7 days after therapeutic dose. Patients will have to stay hospitalized between 3 and 7 days after injection, depending on received radioactivity, Patients will be discharged when 1-m rate of exposure reaches <40μSievert.h^− 1^.

The biodistribution of [^131^I]ICF01012 will be assessed using Whole-body planar scintigraphy acquisition (4 days (D15 ± 4 days), 7 days (D18 ± 4 days), 14 days (D25 ± 4 days), 63 days (D74 ± 4 days) after therapeutic injection) and SPECT-CT acquisition 4 days after injection (D15 ± 4 days) and SPECT at D77 days (D18 ± 4 days) 14 days (D25 ± 4 days), 63 days (D74 ± 4 days) after therapeutic injection. Blood and urine tests for safety evaluation will be performed 1 day, 4 days, 5 days and 7 days after therapeutic dose.

##### Follow-up

Non-eligible patients for therapeutic part will be followed during 3 weeks: 2 follow-up visits are scheduled 14 days and 35 days after diagnostic dose injection for safety evaluation (clinical examination, vital measurement, blood and urinary analyses, specialized consultations (ophthalmologist, neurologist and dermatologist)).

For patient receiving the therapeutic dose, five follow-up visits are scheduled 14, 28, 42, 63 and 85 days after therapeutic dose injection. Each visit will include: clinical examination, vital measurement, blood and urinary analyses. Specialized consultations (ophthalmologist, neurologist and dermatologist) will occur 14 days after therapeutic dose and for dermatologist consultations 42 and 85 after therapeutic dose. Dosimetric acquisitions will be done on 14 and 63 after therapeutic dose (see below). Post-therapeutic cardiac evaluation (myocardial perfusion scintigraphy) and disease staging (cranial and thoraco-abdominopelvic CT scan and [^18^F] FDG PET-CT) will be done 85 days after therapeutic dose.

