#### Secondary objectives

The secondary objectives and the corresponding end-points are:To determine the [^131^I]ICF01012 sensitivity and specificity in a patient-based analysis and in a lesion-based analysis.[^131^I]ICF01012 sensitivity and specificity in patient-based analysis and in lesion-based analysis will be quantified by comparison of visualized or non-visualized lesions with [^131^I]ICF01012 imaging compared to metastatic lesions objectified by standard imagery (TEP-TDM or TDM) and or clinical evaluation.To evaluate the tolerance of [^131^I]ICF01012. [^131^I]ICF01012 tolerance (acute and delayed toxicities) will be evaluated with the Common Terminology Criteria for Adverse Events (CTCAE, version 4.03) with a special consideration for skin-related, ocular and neurological toxicities. Tolerance assessments include: Clinical examination with vitals (heart rate, blood pressure, temperature, respiratory rate), weight, height, OMS performance status; Cardiac evaluation (myocardial perfusion scintigraphy with measure of left ventricular ejection fraction (LVEF), Electrocardiogram (ECG); Specialised consultation with dermatologist, neurologist and ophthalmologist (with of a dilated fundus examination); Blood test including Fool blood count, prothrombine time, factor V, sodium, potassium, chloride, calcium, phosphore, bicarbonate, serum total protein, serum albumin, fasting blood glucose level, Thyroid-stimulating hormone (TSH), free thyoroxine (fT4), free triiodothyronine (fT3), creatinine, urea, bilirubin, Alkaline phosphatase (ALP), Gamma-glutamyltransferase (GGT), Aspartate amino transferase (AST or SGOT), Alanine amino transferase (ALT or SGPT), Troponin Lactate dehydrogenase (LDH); 24-h urine collection tests: glucose, urea, creatinine, albumin, sodium, potassium, magnesium, calcium, protein electrophoresis. Reporting of serious adverse events and suspected unexpected serious adverse reaction will be carried out according to the local regulations.To evaluate the pharmacokinetics of [^131^I]ICF01012 including the study of biodistribution and excretion.Variations of [^131^I]ICF01012 radioactivity concentration (AUC, Tmax and Cmax) will be measured on whole blood plasma during 8 days after diagnostic dose. Plasmatic free fraction of [^131^I]ICF01012 will be quantified by radioactive counting for each patient.24-h urinary excretion will be measured by counting.The biodistribution will be assessed with planar scintigraphy by measuring the percentage of [^131^I]ICF01012 injected dose absorbed by target and non-target organs for both diagnostic and therapeutic doses.To assess the therapeutic response of [^131^I]ICF01012. Therapeutic response (objective response rate, rate of clinical benefit, progression-free survival) will be assessed by TDM according to RECIST 1.1 criteria and by [^18^F] FDG TEP/TDM according to PERCIST criteria.To evaluate the correlation between therapeutic response, injected dose and tumoral uptake.To evaluate the personalized dosimetry applied to [^131^I]ICF01012, and its interindividual variability, Absorbed dose for each organ will be assessed by MIRD formalism.To compare the therapeutic recommended dose with the dose calculated with personalized dosimetry;To compare biodistribution of diagnostic dose and therapeutic dose.

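### Table 2, the schedule for treated patients, contradicts the text on pharmacokinetic sampling after 3 h and on what the follow-up visits contain, including day 28 inside the DLT window

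*Protocol article*

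**What the plan says.** The section Study procedures and participant timeline assigns Table 1 to patients who have only the selection part and Table 2 to those who go on to treatment.

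**Pharmacokinetics.** Under Secondary objectives, AUC, Tmax and Cmax "will be measured on whole blood plasma during 8 days after diagnostic dose". The Selection part section, which covers every patient, runs the sampling from 5 min through "3 h (D0) 24 h (D1), 96 h (D4) and 168 h (D7) post-injection". Table 1 agrees, with entries at D0, D1, D4 and D7. In Table 2 the row has a single entry, at D0: "Before, 5, 10, 15, 30 min, 1 h, 3 h after".

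**Follow-up of treated patients.** The Follow-up section states that "five follow-up visits are scheduled 14, 28, 42, 63 and 85 days after therapeutic dose injection", and then "Each visit will include: clinical examination, vital measurement, blood and urinary analyses". Of the specialist consultations it says they "will occur 14 days after therapeutic dose and for dermatologist consultations 42 and 85 after therapeutic dose". Table 2 leaves several of the promised items blank at D39 and D74, and adds an ophthalmologist visit at D96.

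**Safety laboratory tests.** The Selection part section asks for blood and urine tests at D4 and D7. The Therapeutic part section asks for them 1, 4, 5 and 7 days after the therapeutic dose.

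**The concern.** Text and table are both operative schedule rules, and where they differ they cannot both be followed.

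Two of the differences touch endpoints. The AUC is defined over 8 days, and a schedule that ends at 3 h cannot supply it. The primary endpoint rests on DLTs within 6 weeks of the therapeutic dose, in a CRM with cohorts of one patient and at most 18 treated patients. Each patient's DLT status therefore carries weight, and the scheduled examinations inside the window should be the same for everyone.

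The pharmacokinetic mismatch also has a practical side. Eligibility for treatment is checked from D4 until D7, so at D1 a site cannot tell which of the two tables applies to the patient.

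**Working it through.** No figure in the plan needs reproducing. The check sets Table 2 against the text cell by cell.

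**1. Alignment.** Table 2 has 16 timepoint columns (screening to D96), and each row compared here has 16 cells, so the blanks fall in identifiable columns. The therapeutic dose is at D11 (± 4). Adding the text's visit days gives 11 + 14 = D25, 11 + 28 = D39, 11 + 42 = D53, 11 + 63 = D74 and 11 + 85 = D96. These are exactly the follow-up columns of Table 2, so D39 is the day-28 visit and D74 the day-63 visit.

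**2. Pharmacokinetic samples.**
- Text: 5, 10, 15, 30 min, 1 h, 3 h, 24 h, 96 h, 168 h = 9 post-dose samples.
- Table 1: the same times, with D1, D4 and D7 ticked.
- Table 2: 5, 10, 15, 30 min, 1 h, 3 h = 6 post-dose samples; the other three are absent.
- Coverage under Table 2: 3 of 168 h, or 3/168 = 1.8% of the sampled interval.

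The imaging row of Table 2 does show D1, D4 and D7, so those columns were not lost in that table.

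How much AUC lies within 3 h depends on the plasma half-life, which the article does not give. As an illustration only, assume mono-exponential decline with half-life h. The share of the 0–168 h AUC seen by 3 h is (1 − 2^(−3/h)) / (1 − 2^(−168/h)): 50% for h = 3 h, 29% for 6 h, 8% for 24 h, 5% for 48 h. A fast distribution phase would raise these shares. Cmax and Tmax are another matter: after an injection of about 10 min, the D0 samples largely capture the peak.

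**3. Follow-up visits.** Items promised by the text at every visit, against the Table 2 entries:

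| Visit | Examination | Vital signs | Blood | Urine |
|---|---|---|---|---|
| D25 (day 14) | yes | yes | yes | yes |
| D39 (day 28) | **no** | **no** | yes | yes |
| D53 (day 42) | yes | yes | yes | yes |
| D74 (day 63) | yes | **no** | **no** | **no** |
| D96 (day 85) | yes | yes | yes | yes |

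Five of 20 cells disagree, in two of the five visits.

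**4. DLT window.** The window is 6 × 7 = 42 days. With D39 blank, the scheduled physical examinations nearest to it are at days 14 and 42, a nominal gap of 42 − 14 = 28 days inside the window. D74 and D96 lie outside it.

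**5. Ophthalmology.** The text's only ophthalmology visit in follow-up is at day 14; Table 2 adds day 85. The last scheduled eye check therefore differs by 85 − 14 = 71 days between the two.

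**6. Laboratory tests.** Urinalysis at D4 and D7 appears in the text but in neither table: Table 1 has it at screening, D14 and D35 only, and Table 2 has none between screening and D11. On the day after the therapeutic dose (D12), Table 2 has chemistry and urinalysis but no haematology, although Secondary objectives lists a full blood count among the blood tests.

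**The case against.** The strongest reply is that the blanks are probably omitted ticks. The text states the late pharmacokinetic samples for every selection-part patient, Table 1 repeats them, and the 8-day endpoint needs them. At D1, and usually at D4, the site does not yet know that Table 2 will apply. The article also condenses an approved protocol (version 7) that is not shown, so the schedule that sites hold may be correct. All of this bears on how likely the loss is. It does not remove the contradiction in the document as printed.

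A reader might infer three stronger claims, and the documents do not support them:

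- *The pharmacokinetic objective fails.* That would require sites to set aside the endpoint definition, the Selection part text and Table 1 together. Even then Cmax and Tmax would largely survive, and any percentage of AUC lost rests on an assumed half-life.
- *DLTs between days 14 and 42 would go unseen, or nothing is checked at day 28.* Table 2 keeps haematology, chemistry, thyroid function and urinalysis at D39, collects adverse events throughout, and has a full visit at day 42. The 28 days are a gap between scheduled physical examinations, not a gap in DLT ascertainment.
- *The D74 and D96 differences affect the primary endpoint.* Both visits fall after the DLT window. The D96 ophthalmology visit is an addition in the table and loses no data.

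**Conclusion.** The contradictions are real and can be read directly from the printed schedule. This is a minor to moderate internal inconsistency, not a flaw in the design.

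Two items matter most. The Table 2 pharmacokinetic row, if followed, would leave the 8-day AUC without data after 3 h in the treated patients. The missing examination and vital signs at D39 would make ascertainment of non-laboratory DLTs weaker between days 14 and 42, and uneven if some patients were followed by the text and others by the table. The D74, D96, D4/D7 urine and D12 haematology mismatches concern secondary safety data or early laboratory checks and are smaller.

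The size of the first two items is conditional on Table 2 being followed literally, which the article does not establish.

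**What to change.** - Add the D1, D4 and D7 pharmacokinetic samples to Table 2, as the Selection part text, Table 1 and the AUC window ("during 8 days after diagnostic dose") require.
- Reconcile the D39, D74 and D96 contents of Table 2 with the Follow-up section, so that scheduled examination within the DLT window is the same for every treated patient. The same pass should settle whether ophthalmology ends at day 14 or day 85.
- Reconcile both tables with the Selection part text on urine tests at D4 and D7, and Table 2 with the Therapeutic part text on haematology at D12.

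Do not do this by making the D0–D7 columns of the two tables identical. The optical coherence tomography that Table 2 shows at D7 applies only to patients eligible for treatment, and identical columns would not restore the D4/D7 urine test, which both tables lack.

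The cost is a table correction; every sample and visit concerned already stands somewhere in the document. Compare first with the schedule in the approved protocol. If it carries the same blanks, check whether any patient already treated was followed by them, since the trial is recruiting.
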